## Abstract

**Introduction:**

Outpatient parenteral antimicrobial therapy (OPAT) is used to treat a wide range of infections, and is common practice in countries such as the USA and Australia. In the UK, national guidelines (standards of care) for OPAT services have been developed to act as a benchmark for clinical monitoring and quality. However, the availability of OPAT services in the UK is still patchy and until quite recently was available only in specialist centres. Over time, National Health Service (NHS) Trusts have developed OPAT services in response to local needs, which has resulted in different service configurations and models of care. However, there has been no robust examination comparing the cost-effectiveness of each service type, or any systematic examination of patient preferences for services on which to base any business case decision.

**Methods and analysis:**

The study will use a mixed methods approach, to evaluate patient preferences for and the cost-effectiveness of OPAT service models. The study includes seven NHS Trusts located in four counties. There are five inter-related work packages: a systematic review of the published research on the safety, efficacy and cost-effectiveness of intravenous antibiotic delivery services; a qualitative study to explore existing OPAT services and perceived barriers to future development; an economic model to estimate the comparative value of four different community intravenous antibiotic services; a discrete choice experiment to assess patient preferences for services, and an expert panel to agree which service models may constitute the optimal service model(s) of community intravenous antibiotics delivery.

**Ethics and dissemination:**

The study has been approved by the NRES Committee, South West—Frenchay using the Proportionate Review Service (ref 13/SW/0060). The results of the study will be disseminated at national and international conferences, and in international journals.

Strengths and limitations of this studyA key outcome of this study will be an understanding of patient preferences for services.An economic model evaluating the value-for-money of outpatient parenteral antimicrobial therapy (OPAT) services.The potential beneficiaries of the research are National Health Service (NHS) Trusts and those responsible for commissioning services as this will provide a robust evidence base on which to make service provision decisions.Policy makers charged with developing national guidelines for services would benefit from the knowledge generated and this would be reflected by well-informed, evidence-based guidance on the relative value of different service configurations.While not a clinical trial, this study offers insights into the cost-effectiveness of OPAT services, and provides evidence on which decisions relating to the conduct of any future randomised controlled trial could be based.

## Introduction

To meet the challenges of delivering quality healthcare, health systems must continue to develop programmes that deliver safe, high-quality, cost-effective patient care.^1^ Delivery of intravenous antibiotics to patients outside a hospital setting—often termed outpatient parenteral antimicrobial therapy (OPAT)—was first described on a small scale in the 1970s in North America. By the end of the 1990s, an estimated quarter of a million patients annually were receiving intravenous antibiotics on an outpatient basis due to a range of factors, including cost savings, patient preference, better intravenous devices, the introduction of antimicrobial agents which only needed administration once or twice a day and the introduction of new OPAT services.^2^ A wide variety of infections have been treated through this system, in particular skin and soft tissue infections,^3^ but also infections such as osteomyelitis,^4^
^5^ bacteraemia^6^ and endocarditis.^6^ Although widely accepted as the standard of care in countries such as the USA and Australia, such services are largely limited to patients with appropriate health insurance cover.^7^

OPAT services in the UK started in the 1990s, and were limited to specialist centres, but services have recently began to expand, as the benefits to patients and the healthcare system were recognised.^2^ Several countries, including the UK have developed national guidelines (standards of care) for OPAT services to act as a benchmark for clinical monitoring and quality.^2^
^8^
^9^ To support the development of such services in the UK, the British Society of Antimicrobial Chemotherapy (BSAC) have sponsored the development of a toolkit which clinicians can use to develop a business case for their service. This toolkit contains SWOT analyses for each service type, but does not favour any particular model of service design.^2^ Indeed, there has been no robust examination comparing the cost-effectiveness of each service type, or any systematic examination of patient preferences for services on which to base any business case decision. Further barriers to the development of OPAT services are a lack of any specific funding system for this in the National Health Service (NHS), combined with the complexity of existing charging mechanisms.^10^

### Clinical practice in the UK

Nevertheless, in recent years, OPAT services have developed in some areas of the UK both in the NHS and private sectors, largely in response to local pressures in combination with healthcare staff initiatives.^11^ This has led to many service variations using different heathcare professionals which can be grouped into four main categories: (1) daily attendance at a hospital outpatient facility (or community-based clinic); (2) self-administration or carer administration in the patient's own home; (3) provided by community nurses with general skills, for example, district nurses in the patient's own home; (4) provided by specialist nurses, for example, NHS or private nursing teams, in the patient's own home.

## Methods and analysis

### Study objectives

Evaluation of the existing evidence of efficacy, safety and cost-effectiveness of different intravenous antibiotic services.Assessment of current OPAT provision by the NHS by establishing reasons for current service configuration and identifying barriers to service provision.Economic modelling of the different delivery systems to evaluate their cost-effectiveness in both short-term and longer term infection patient groups.Determination of patient preferences for different community intravenous antibiotic service attributes through a discrete choice experiment (DCE).Hold an expert panel to agree on what may constitute the optimal service model(s) of community intravenous antibiotics delivery and how future clinical trials should be designed to test these services.

### Design

The study will use a mixed methods approach, combining qualitative and quantitative methodologies in five interconnected work streams. A systematic review of the published research on the safety, efficacy and cost-effectiveness of intravenous antibiotic delivery services; a qualitative study undertaking semistructured telephone interviews with 25–30 healthcare professionals managing intravenous antibiotic services in England exploring models of service offered and any perceived barriers to future development; an economic model to estimate the comparative value of four different community intravenous antibiotic services (described above) and allow comparisons of the expected costs and benefits of each service for both short-term and longer term infection patient groups. We will model the costs and benefits of running several services concurrently and providing patients with choices. Determining patient preferences using a DCE will inform which aspects of treatment are important to patients and which they would prefer in the future. Patients will be sampled from those with short-term infections having less than a week of treatment (eg, cellulitis) and those with deeper infections requiring longer treatment (eg, bone infections). The development of the DCE will involve semistructured interviews with patients and will incorporate any relevant literature. Lastly, an expert panel with a range of stakeholders to agree which service models may constitute the optimal service model(s) of community intravenous antibiotics delivery, and which are worthy of testing in clinical trials and to discuss trial design issues.

### Setting

The research will be conducted in seven acute trusts; four in West Yorkshire, one in East Yorkshire, one in South Yorkshire and one in Oxford.

### Systematic review

The aim of the review is to evaluate the existing evidence of efficacy, safety and cost-effectiveness of different intravenous antibiotic services.

There are no existing relevant systematic reviews of this topic, and this work is not an update of an existing systematic review.

Questions to be considered:
What is the most clinically effective model of delivering intravenous antibiotics in the community?What is the most cost-effective model of delivering intravenous antibiotics in the community?What is the most appropriate model for delivering intravenous antibiotics in the community in terms of patient safety?Is community delivery of intravenous antibiotics acceptable to patients and care providers?

#### Searches

Two searches will be run to identify (A) studies of intravenous antibiotics and known models of care, (B) reviews of intravenous antibiotics in cellulitis or cystic fibrosis. The aim of search B is to retrieve papers mentioning models of care that we were unaware of when identifying terms for search A. A range of information sources will be searched: Bibliographic databases: MEDLINE, Medline in process, EMBASE, CINAHL, International Pharmaceutical Abstracts. The Cochrane Library, Cochrane Library evidence resources: Cochrane Database of Systematic Reviews, Cochrane Central Register of Controlled Trials. Economics resources: NHS Economic Evaluation Database, Research Papers in Economics (RePEc), Tufts Cost-Effectiveness Analysis (CEA) Registry, Health Business Elite (HBE).

Supplementary searches of Web of Science Proceedings, the Health Information Management Consortium (HMIC), International Pharmaceutical Abstracts and the website of the British Society for Antimicrobial Chemotherapy will be conducted to provide relevant unpublished work. In addition, the reference lists of included studies will be reviewed for potentially relevant papers. A sample search strategy is detailed in appendix A. The period under review is 1993–2013 (with updates planned before the submission of the final report). No language restrictions will be applied.

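### Search B, the only database search aimed at unknown service models, leaves out bone and other deep infections, so a model described mainly in that literature may be missed

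*Protocol article*

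**What the plan says.** The Searches section of the Protocol article sets out two searches. The first covers "A) studies of intravenous antibiotics and known models of care". The second covers "reviews of intravenous antibiotics in cellulitis or cystic fibrosis". The section gives the second a specific purpose: "The aim of search B is to retrieve papers mentioning models of care that we were unaware of when identifying terms for search A". It does not say why those two conditions were chosen, and cystic fibrosis is mentioned nowhere else in the article.

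The Design section divides patients into two groups. One is "those with short-term infections having less than a week of treatment (eg, cellulitis"), the other "those with deeper infections requiring longer treatment (eg, bone infections"). The Introduction says that outpatient intravenous treatment has been used most notably for skin and soft tissue infection, "but also infections such as osteomyelitis", and goes on to name bacteraemia and endocarditis.

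The Searches section also plans to check the reference lists of included studies and to search conference proceedings, two further databases and a professional society's website for unpublished work. An update of the searches is planned before the final report.

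**The concern.** Search A is limited by model and search B by disease. A service model that the team did not know, and that is reported mainly in the literature on bone infection, endocarditis or bacteraemia, can fall outside both. Search B is the one intended to guard against unknown models, yet its disease terms match only one of the two patient groups by the protocol's own examples.

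The review has no language restriction and is not confined to one country, so it is the part of the study best placed to find a model not in use in England. Its results go to the DCE and the expert panel, and the panel must reach a view for the longer-term group as well as the short-term one. The data extraction form has a category for models other than the four listed, but it can record only what the searches bring in.

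**Working it through.** No arithmetic applies: the article gives no hit counts and no figure on this point. The check sets the sections side by side.

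**1. What each database search can reach (Searches)**

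| | Limited by model? | Limited by infection? | Can reach an unknown model in cellulitis? | Can reach an unknown model in bone infection? |
|---|---|---|---|---|
| Search A | Yes, known models | None stated | Not by design | Not by design |
| Search B | No | Yes, two conditions | Yes | Not by its stated terms |

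That search A has no infection limit means it should find deep-infection studies of the known models. It does not help with unknown ones.

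**2. Match to the patient groups (Design)**

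- Short-term example, cellulitis: in search B.
- Longer-term example, bone infection: not in search B.
- Cystic fibrosis: in search B, but assigned to neither group in the article.

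**3. Match to the infections named in the Introduction**

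Four types are named: skin and soft tissue infection, osteomyelitis, bacteraemia and endocarditis. Search B touches the first, through cellulitis, and none of the other three. This count describes scope. It does not measure lost papers.

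**4. Other routes by which an unknown model could be found**

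- Reference lists (Searches): no infection limit, but they start from studies already included.
- Supplementary searches (Searches): no infection limit stated, but aimed at unpublished work.
- Service survey and the 25–30 staff interviews that follow it (Qualitative study): not limited by infection, but the survey maps provision in England.
- Patient focus groups and interviews, 30–50 adults (DCE, Phase 1): sampled to span treatment lengths and services, but the participants are people who have already had community treatment.

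Each route narrows the gap. None is a search of the published international literature for unknown models in deep infection.

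**5. What depends on search B**

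- Economic model: it compares four services fixed in advance. The target of 400 records is 50 per cell × 2 infection types × 4 models = 400, which leaves no cell for a fifth model. The review supplies parameter values for the four, and studies of known models are what search A is for.
- DCE: attributes are built from the patient focus groups and interviews. The literature also informs the survey content.
- Expert panel: it considers the review alongside the service survey, the DCE and the economic model.

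A gap in search B can therefore weaken the review and what it passes to the DCE and the panel. It does not alter the planned four-way cost-effectiveness comparison.

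**The case against.** The strongest reply is that harm needs several things to coincide. The article defines models by who gives the treatment and where, not by infection. To be lost, a model would have to be described mainly in deep-infection papers, in terms search A does not use, and be absent from the reference lists, the supplementary sources, the surveyed specialists and the interviewed patients. No such model is known from the document. Search B also reads as a probe for unfamiliar models rather than an attempt at full coverage. The sample strategy in appendix A and the registered review protocol are not shown and may explain the choice of conditions.

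Much of this stands, and it is why the point is minor. It also rules out stronger readings that a reader might infer:

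- That search B is the only route to unknown models. It is the only database search given that aim, but the article plans at least four other routes.
- That a missed model would never reach the DCE or the panel. The DCE attributes come mainly from patients across treatment lengths, and the panel sees the service survey.
- That the longer-term group is wholly uncovered. Cystic fibrosis may have been meant to stand for longer courses. The article does not say so, but it does not exclude it.

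What the reply does not answer is the mismatch in the text itself. The article states the scope of search B outright, so this is not a detail left to a fuller document, and that scope omits the protocol's own example of one of its two patient groups.

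**Conclusion.** The point holds as a minor mismatch between the aim of search B and its scope. A published model described mainly in the deep-infection literature, particularly one used outside England, may be missed by both database searches unless another planned route finds it.

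The size cannot be given as a number of papers or models. The reach is limited to the review and the evidence it passes to the DCE and the expert panel. A reader might infer that the cost-effectiveness results are at risk. They are not on this account, because the four services compared are fixed whatever search B finds.

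The conclusion rests on two assumptions: that the search was run as the article words it, and that some models may be reported more in one infection's literature than in another's. The document neither supports nor excludes the second.

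**What to change.** Add reviews of intravenous antibiotics in bone and joint infection, including osteomyelitis, to search B, and keep cellulitis and cystic fibrosis. Add endocarditis and bacteraemia if the screening load allows. If the first search has been run, run the additions at the update already planned before the final report.

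The change needs a few search terms. Its downside is more review abstracts for the existing screeners, where one reviewer screens all abstracts and a second screens a random 20%.

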#### Criteria for selection of studies

Studies will be eligible for inclusion if the participants are individuals or groups of adult patients or care providers *and* they evaluate the clinical effectiveness or cost-effectiveness of an OPAT model, *or* they describe or evaluate patient safety issues associated with OPAT, *or* they consider the acceptability of OPAT from the perspective of the patient receiving treatment or the practitioner delivering care. Any form of intravenous delivery system will be included (eg, infusion or bolus).

Studies will be excluded if they make reference to clinical effectiveness but do not report on specific patient outcomes. Similarly, studies that consider costs related to a model of delivery without considering patient benefit alongside these, and studies making reference to costs and benefits without reporting specific cost-effectiveness data (eg, cost per quality-adjusted life year (QALY)) will also be excluded. Studies that include children will be reviewed but excluded if they do not report outcomes for adult patients separately. Studies involving multiple routes of delivery of antibiotics will be reviewed but will be excluded if they do not report outcomes for patients receiving intravenous treatment separately.

The outcomes of interest are clinical effectiveness (cure or improvement, duration of treatment), cost-effectiveness (cost, benefit), safety (complications, adverse events, hospital admission), patient acceptability and provider acceptability.

Both experimental (randomised controlled trials, controlled clinical trials, controlled before and after studies) and non-experimental (case–control, cohort, cross-sectional, other observational) studies will be included. Quantitative, qualitative and mixed-methodology studies will be included.

The review and synthesis of data will be undertaken in accordance with the Centre for Reviews and Dissemination guidelines for systematic reviews.^12^ A protocol of the review was produced and added to the PROSPERO database (CRD ref: 4201300637 4).

#### Data extraction

Abstracts of all identified studies will be screened for inclusion by one reviewer with a random selection (20%) independently screened by a second reviewer. Potentially relevant studies will then be independently assessed by two reviewers to determine whether they meet the inclusion criteria. Differences of opinion will be discussed until a consensus is reached; the opinion of a third reviewer will be sought where necessary.

Data extraction will be carried out by one reviewer using a standardised proforma. Extracted data will include citation details, study purpose, design, location, setting, duration, population details and clinical characteristics (reason for antibiotic treatment), models of care (outpatient, self-administration, general nurse, specialist nurse or other), topic area (clinical effectiveness, cost-effectiveness, safety, acceptability), type of antibiotic, route of delivery, treatment dose, outcome measures (if relevant), follow-up and key findings.

#### Quality assessment

Quality assessment will be carried out by one reviewer. The Cochrane Risk of Bias assessment tool will be used for experimental studies, and the Newcastle-Ottawa scales for cohort and case–control studies.^12^
^13^ We will use critical interpretive synthesis developed by Dixon-Woods *et al*^14^ to review and analyse any qualitative literature. The quality of studies reporting economic evaluations will be assessed using the Drummond *et al*^15^ checklist. Studies will be selected by two researchers working independently with inconsistencies resolved following discussion.

Studies at risk of bias will not be excluded from the review, but an appraisal of the strength of existing evidence will be reported, and the review findings interpreted in light of this.

#### Evidence synthesis

The main characteristics of included studies and findings relating to clinical effectiveness, cost-effectiveness, patient safety and acceptability, and study quality will be summarised in narrative and tabular form. We anticipate that there will be substantial heterogeneity between included studies, and as such do not plan to pool data for meta-analysis. The synthesised review data will provide values for use in the economic model, DCE and evidence for consideration by the expert panel.

### Qualitative study

The aim of this work package is to assess current NHS OPAT provision by establishing reasons for different service configurations and identifying barriers to service provision.

#### Design: qualitative telephone interviews

Initially, a brief electronic or telephone survey will be administered to infection unit managers and/or infection specialists to establish types of services available in England. This will be used to identify potential interviewees.

#### Sampling

Purposive sampling via a sampling matrix will recruit participants with different experiences of delivering OPAT services. A sample of 25–30 infection specialists and/or unit managers will be recruited. This will ensure a detailed and comprehensive range of perspectives and participants.

#### Data collection

Semistructured, telephone interviews will be conducted using a topic guide developed from the literature review and expert opinion (clinician co-applicants/advisors and Patient and Public Involvement (PPI) members). The researcher will probe pertinent initial responses and expand on issues raised. Interviews will be recorded and transcribed verbatim.

